## Abstract

**Background:**

Infants with unilateral brain lesions are at high risk of developing unilateral cerebral palsy (CP). Given the great plasticity of the young brain, possible interventions for infants at risk of unilateral CP deserve exploration. Constraint-induced movement therapy (CIMT) is known to be effective for older children with unilateral CP but is not systematically used for infants. The development of CIMT for infants (baby-CIMT) is described here, as is the methodology of an RCT comparing the effects on manual ability development of baby-CIMT versus baby-massage. The main hypothesis is that infants receiving baby-CIMT will develop manual ability in the involved hand faster than will infants receiving baby-massage in the first year of life.

**Method and design:**

The study will be a randomised, controlled, prospective parallel-group trial. Invited infants will be to be randomised to either the baby-CIMT or the baby-massage group if they: 1) are at risk of developing unilateral CP due to a known neonatal event affecting the brain or 2) have been referred to Astrid Lindgren Children’s Hospital due to asymmetric hand function. The inclusion criteria are age 3–8 months and established asymmetric hand use. Infants in both groups will receive two 6-weeks training periods separated by a 6-week pause, for 12 weeks in total of treatment. The primary outcome measure will be the new Hand Assessment for Infants (HAI) for evaluating manual ability. In addition, the Parenting Sense of Competence scale and Alberta Infant Motor Scale will be used. Clinical neuroimaging will be utilized to characterise the brain lesion type. To compare outcomes between treatment groups generalised linear models will be used.

**Discussion:**

The model of early intensive intervention for hand function, baby-CIMT evaluated by the Hand Assessment for Infants (HAI) will have the potential to significantly increase our understanding of how early intervention of upper limb function in infants at risk of developing unilateral CP can be performed and measured.

**Trial registration:**

SFO-V4072/2012, 05/22/2013

## Background

Recent knowledge of the great plasticity of the young brain indicates that it is important to start training at an early age. There have so far been no early-intervention programmes designed to improve hand function in infants with cerebral palsy (CP); most programmes have instead targeted general motor and cognitive development [1,2]. Existing studies of early intervention mainly cover preterm infants, sometimes even excluding children with CP because of its heterogeneity. One reason for the lack of established intervention programmes for hand use in infants, is uncertain diagnosis. The most accurate predictive tool for CP is brain imaging combined with Prechtl’s Assessment of General Movements administered up to 4 months post term [3-5]. However, many children with unilateral CP are born at term with no adverse birth events. Whether or not there is a suggestive neonatal history, obvious signs of unilateral CP usually do not appear until 4–5 months of age. Unilateral CP is a common subtype of CP and brain imaging reveals that white-matter lesions and cortical/subcortical lesions are the commonest types of brain lesions [6]. However, brain lesions do not necessarily result in CP; for example, only approximately 30% of all children with neonatal stroke will eventually develop unilateral CP [7], and even haemorrhages and other incidents in preterm children do not necessarily lead to CP [5]. This makes it difficult to decide which children might benefit from early-intervention programmes.

In recent decades it has become clear that hand function can be improved by active motor training in older children [8,9]. Modified constraint-induced movement therapy (CIMT), an effective method for such training, is based on constraint of the non-involved hand and intensive activity-based training of the impaired hand. Before CIMT should be used for infants, however, it needs to be tested for feasibility and its dosage and degree of restraint adjusted to suit young infants. More importantly, no available assessments describe signs of or monitor hand use development in such young infants. This paper describes a special adjustment of the intervention method, baby-CIMT, to be used in an RCT evaluated using our newly developed Hand Assessment for Infants (HAI) to measure hand function in each hand separately and both hands together.

### Translation of learning-induced brain plasticity into clinical practice

Early intervention is expected to be important, as neural networks and pathways that remain intact after brain injury can be strengthened through learning-induced plasticity. After Hubel and Wiesel’s ground-breaking discoveries of visual system plasticity in the 1970s, Nudo et al. [10] demonstrated that neural activity induces synaptic changes in the sensory and motor cortex. The corticospinal system also experiences ongoing structural change [11-13]. More recent animal studies have demonstrated that there is a critical period of motor system plasticity, and that activity-dependent reorganisation of the motor-projection pattern to the hand occurs before about 1 year of age [14,15]. Activity-based training using a model of CIMT synchronised with the development of the corticospinal tract in an animal model of CP restored motor function and induced structural changes in the corticospinal system [16,17]; this restoration was not found if the intervention was implemented at a higher age. Increased knowledge of early brain plasticity supports increased interest in early intervention and its impact on the development of the hand motor system. In this project, we would like to exploit the great plasticity of the young brain, hypothesising that treatment at an early age will influence the future level of development. This hypothesis is based on the assumption that there are critical periods during human brain development in which treatments are more effective than they would be later on.

### Object exploration and manipulation in the first year of life

To evaluate any hand training programme for infants, it is important to have a good understanding of the natural history of hand development in young children. Voluntary action starts to emerge at birth, and von Hofsten [18] has demonstrated that reaching and grasping actions can be detected even in newborns, though it takes some months before grasping actions are obvious and frequent. In the first year of life, infants gradually gain remarkable control over their hands, exploring and manipulating objects with increasing skill [19]. Infants consciously explore objects, typically using the hand nearest an object or both hands together [20]. There is typically no asymmetry or hand preference before about 9 months of age in typically developing children [21], nor is coordinated bimanual hand use seen until about 8 months of age, when infants start performing more complex sequences, such as removing a lid to grasp a toy [22]. Typically developing infants use both hands equally.

### Early hand motor function in children with unilateral CP

The development of hand use below the age of 12 months in infants with unilateral CP has not been described. It is not known when deviation from normal development can first be detected nor what the typical signs of unilateral CP might be. Textbooks usually describe unilateral CP as characterized by a flexed elbow, pronated forearm, and thumb in the palm without applying a developmental perspective. We have recently started to monitor infants from early ages who are likely to develop unilateral CP and it is clear that the amount and quality of hand use develops differently in the two hands at an early age. Asymmetric hand use can already be seen at the age of 3–5 months. Using our newly developed instrument, HAI for infants aged 3–12 months, we can for the first time describe and measure this difference from typical early motor development ([name] et al., in preparation). HAI measures each hand separately in uni- and bimanual play-tasks. This means that HAI will fill an important gap, because no currently available outcome measure can quantify the development of asymmetric hand function at such a young age, and available norm-referenced tests do not reflect the deviant development seen in children with unilateral CP [23,24]. Based on our ongoing research, we know that variation among infants is considerable and that developmental differences range from negligible to dramatic during the first year of life.

### Theoretical assumption for intervention

Two types of interventions based on different theoretical assumptions will be tested in this project. Briefly stated, the CIMT programme for infants (baby-CIMT) is based on self-initiated action and assumes that one must practice the motor action one intends to learn. The baby-massage intervention is based on the assumption that general tactile stimulation is important for development. Both interventions assume that early stimulation is important; by using baby-massage as a comparison group, we can control for the placebo effect of increased attention and time spent with the child. The theoretical assumptions and evidence supporting both methods will be described in greater depth.

#### Baby-CIMT

CIMT is characterized by restraint of the well-functioning upper limb (irrespective of restraint device/type) and intensive structured training (irrespective of training type) [25]. CIMT needs further development and adjustment to be appropriate and feasible for infants. Baby-CIMT has been developed in our research group and its modification will be described for the first time here. Baby-CIMT is a manual motor training programme shaped by several important perspectives on infant development with the general aim to increase the amount and quality of hand use.

The assumption underlying baby-CIMT, as in the case of the original CIMT model, is that the practice of self-initiated motor actions is crucial for motor development. The theoretical perspectives that have shaped the baby-CIMT programme are pretty similar to those that shaped the eco-CIMT programme for children above 2 years of age [26]. The baby-CIMT play session, i.e., the active motor training, is influenced by dynamic systems theory, a model highlighting the importance of children’s self-initiated activity [27]. From this perspective, we assume that development is driven by children’s unique characteristics and capacity to explore the environment, through which they discover new abilities. This model also emphasises the importance of a rich immediate environment in which a varied selection of toys and other objects facilitates the development process. The principles of motor learning, i.e., how individuals acquire and perform motor activities [28], also underpin baby-CIMT. To promote motor activity in infants, selecting appropriate toys and play objects at just the right ability level is crucial. Repetition is also key, as is feedback on performed behaviour.

Bronfenbrenner and Morris’s ecological model of child development highlights the interaction between the active child and other people, objects, and symbols in the immediate environment [29], suggesting that baby-CIMT must be child centred. Bronfenbrenner and Morris further state that unconditional love and time spent with a child are the two most important agents driving development. This approach, and that of family-centred service (FCS), will guide the present intervention. FCS comprises a set of values, attitudes, and approaches towards the family [30]. When coaching and guiding parents to be the training providers, motivational interviewing [31] and solution-focused coaching [32] are important techniques used by therapists. By using these techniques, therapists can help increase parents’ motivation to be treatment providers and empower them to develop goals and implement the programme. Simply stated, the therapist should ask questions rather than come up with answers; in particular, the therapist must express empathy and build a relationship with the parents. Education will also be part of the programme, and parents’ stress can decrease after they read about and understand the individuality and needs of their infants [33]. Parental education about the infant’s situation is known to enhance cognitive and social function in the infant [34].

#### Baby-massage

Massage is defined as systematic touch by human hands, consisting of gentle, slow stroking of each part of the body in turn. It is often combined with other forms of stimulation, such as kinaesthetic stimulation (e.g., passive extension/flexion of the arms and legs), talking, and eye contact [35]. The overall assumption underlying the baby-massage intervention is that tactile stimulation promotes overall development. The techniques and dosage used vary considerably. Baby-massage is assumed to affect physical health and growth, and factors such as weight gain and body length are expected to be influenced by massage, as are crying and sleeping/waking behaviour [35]. Baby-massage is used for typically developing children in several cultures, and today there is increasing interest in it among parents in western cultures. It is of special interest in neonatal intensive care units (NICU), where the environment can be a stress factor and tactile input can be lacking [36]. There are indications that baby-massage can improve the development of gross and fine motor skills as well as psychomotor development in preterm children [37], a possibility supported by a recent Cochrane review [35]. Children suffering from early brain lesions have been treated with baby-massage in very few studies, one of which found reduced muscle tone and improved fine and gross motor function [38]. It is well known that parent–infant interaction is dependent on parental ability to respond appropriately to the infant’s emotional state. In the fields of developmental psychology and infant mental health, baby-massage is expected to support early parenting and strengthen parent–infant communication [39]. Various mechanisms have been proposed for how massage might benefit infants. The biological rationale for using massage to improve growth and development in preterm or at-risk infants is that it may increase metabolic efficiency while reducing stress behaviour or the production of stress hormones [35]. Baby-massage will be used as an intervention in comparison with baby-CIMT based on its possible effect on motor development but also for its positive effect on parent–infant interaction. Evidence of the long-term benefits of all aspects of baby-massage is still weak, and it would be useful to explore its effects in high-risk infants [35].

## Methods and design

This paper describes the methodology of an RCT comparing the effects of the baby-CIMT and baby-massage protocols on the development of manual ability in infants at risk of developing unilateral CP. The two treatment protocols will be described in detail. HAI was selected as the primary outcome measure with the main aim of measuring the development of manual ability in both hands.

### Ethical considerations

The study has been approved by the Stockholm Regional Ethical Review Board (no. 2009/1100-32). All parents will be given oral and written information about the study before being asked to sign an informed consent form. The randomisation will be performed after the form is signed.

### Primary objective

The primary objective of the study is to investigate the effects of baby-CIMT and baby-massage on the development of manual ability in the first year of life of infants at risk of developing unilateral CP.

The specific hypotheses to be tested are:

1. Baby-CIMT is a feasible method for families and infants below one year of age.

2. Infants receiving baby-CIMT will develop manual ability in the involved hand faster than will infants receiving baby-massage in the first year of life.

3. Improvement of manual ability in the involved hand will be faster during the training period than during a period without training in the baby-CIMT group.

4. The manual development of the involved hand will depend on the type of brain lesion. Infants born at term with neonatal stroke are expected to develop more slowly than will preterm infants with mainly white matter lesions, independent of group allocation.

5. Development of manual ability in the non-involved hands will not differ between groups.

6. The assumed difference in manual development in the involved hand at 1 year of age depends on group allocation and the difference will remain at 2 years of age.

The secondary objective is to investigate whether the different treatment protocols influence the parents’ self-rated parenting competence.

1. Parents in the baby-CIMT programme will feel more competent at parenting than will parents in the baby-massage group since they will have learned more about the child’s specific needs.

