### Sample size

The estimated number of participants needed to achieve the study objectives is based on HAI data obtained from a pilot group of 12-month-old infants who received either studied intervention. Based on a two-tailed test of two independent means, with a significance (α) level of 0.05 and 80% power, we require 16 participants in each group for a total sample of 32.

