##### Restraint type and training dosage

Any kind of simple restraint can be used on the non-involved hand. The restraint is only used during the training. From the pilot group we learned that young infants will rarely remove the restraint but will commonly start to use the involved hand as soon as the non-involved hand is rendered less useful by the imposition of a soft restraint. We prefer to keep the restraint simple and comfortable, so a sock or mitt can be used as well as a bag clip at the end of a long-sleeved sweater.

The total dosage will be 36 hours, administered over the two 6-week training periods. The most effective combination of training hours/day and length of training period is currently unknown even for older children [25]. In the present study, we have chosen 30 minutes per day of training based on practical considerations and feasibility. First, the attention span of infants is short: even 30 minutes can be too long and may sometimes need to be divided into two shorter sessions. Second, limited time is available when young infants are alert and awake and this time needs to be shared with other caring needs. To obtain a reasonably high dosage, the length of the programme will be 12 weeks. Parents like to divide the time into two 6-week periods; it gives them time to focus on other things between the periods of treatment and it means that the overall treatment time frame is longer within the first year of life. This longer period takes advantage of the children’s developmental progression in relation to handling toys. Concern has been raised that restraining the non-involved hand may negatively affect its development. This concern will be addressed by means of the short duration of daily restraint and the infants’ continued use of both hands outside the treatment time. We also assume that the infants will immediately start to apply what they learned in the training session at other times of the day. By using HAI as an outcome measure, it will also be possible to monitor the development of each hand separately.

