### Statistical methods

Analyses will be conducted on an intention-to-treat basis. Data for each assessment will be summarised for each treatment group and the descriptive statistics will be calculated depending on the data distribution for each assessment. HAI outcomes will collected at the times defined in the study protocol. The *primary efficacy variable* will be the mean change in the HAI score from baseline to the last post-treatment period after 18 weeks. The *secondary efficacy variable* will be the mean change in the HAI score from baseline to the first post-treatment period after 6 weeks and from baseline to the age of 1 year. The mean change in HAI score will be analysed using ANCOVA, including the baseline as covariate and group as a fixed factor in the model. Another efficacy variable will be the proportions of infants with improved HAI scores from baseline to the first post-treatment period after 6 weeks, to the end of the second treatment period after 18 weeks, and to the age of 1 year. The proportions will be analysed using logistic regression including baseline as covariate and group as a fixed factor. An odds ratio of > 1 will be interpreted as indicating an increased chance of improved HAI score. A significance level of 0.05 will be used.

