## Discussion

This paper outlines the background and design of an RCT with two treatment groups comparing the effects of baby-CIMT and baby-massage. To our knowledge, this is the first study directly investigating the results of specific hand training in this age group. This programme is based on various pilot data collected over several years. In the pilot data, the parents’ responses when their children were older indicated that they felt the programme was feasible. There are some methodological disadvantages to home-administered programs, as the intervention quality and content might vary between families because their situations differ and cannot be controlled for. On the other hand, the advantage for the families is that they do not need to go to hospital frequently and they have learned how to stimulate their child’s hand use in their home environment. In addition, the cost–benefit ratio of such home-based programmes is high, and if baby-CIMT proves to be effective, it can readily be implemented in clinical practice.

The inclusion criteria can be problematic because it is difficult to establish a diagnosis at an early age. If the symptoms are unclear during the first assessment, the infants can be assessed a second time some weeks later to clarify whether the symptoms are still apparent before the child is included in the study. The extent to which asymmetric symptoms may spontaneously disappear at this age is not known, but before inclusion, we will confirm that the parents are observing the same symptoms as we are. If the symptoms disappear, we will not have caused harm and the parents will be reassured about their child. The diagnosis of unilateral CP will be confirmed or discounted at a later age by the child neurologist. We have considered the possibility of CIMT harming the development of the non-involved hand. Although we have not found any interruption to the development of the non-involved hand through our pilot work, we will continue to monitor this matter.

If the study hypotheses are confirmed, this project will be of significant value. Unilateral CP causes limitations that remain throughout the whole life, impacting individual autonomy and the individual’s participation in society. Even small functional improvements may be of great importance to the individual.

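### Hypothesis 5 states no difference in the non-involved hand, but the plan gives only difference tests at 0.05, so non-significance with 16 infants per arm could be misread as no effect

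*Protocol article*

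**What the plan says.** Under Primary objective, the protocol article introduces six numbered statements with "The specific hypotheses to be tested are". The fifth reads "Development of manual ability in the non-involved hands will not differ between groups".

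Statistical methods names ANCOVA for the mean HAI change (group plus baseline) and logistic regression for the proportion improved, then adds "A significance level of 0.05 will be used". It mentions neither hypothesis 5 nor the non-involved hand, and does not say which HAI score enters the model.

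The Sample size section describes its calculation as "Based on a two-tailed test of two independent means" and arrives at 16 infants per group, 32 in all, for 80% power at an α of 0.05.

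Two other places give hypothesis 5 its weight. Restraint type and training dosage notes "Concern has been raised that restraining the non-involved hand may negatively affect its development". The Discussion says "We have considered the possibility of CIMT harming the development of the non-involved hand" and reports no such problem in pilot work. Both places say that this hand will be monitored.

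**The concern.** Hypothesis 5 is a null stated as the thing to be shown. A difference test can reject a null but cannot establish it. A non-significant p-value says only that the data are compatible with zero, and in a small trial they are also compatible with sizeable differences in either direction.

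On most endpoints this would be a point of wording. Here the null concerns the hand that is restrained in one arm only, and the article links that hand to possible harm. If p>0.05 were reported as support for hypothesis 5, readers could take it as reassurance about restraint that the data might not give.

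**Working it through.** **Inputs from the article.** 16 infants per group; two-sided α of 0.05; 80% power; ANCOVA with baseline as covariate.

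**Assumptions.** The article gives no HAI SD, planned difference or baseline correlation. Differences are therefore in units of the within-group SD of the follow-up score, and the correlation ρ between baseline and follow-up is set at 0 (unadjusted), 0.5 and 0.8. No losses are assumed at first.

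**1. The plan's own figure.** Without a difference and SD, the 16 per group cannot be recomputed from the article. It can be solved backwards:

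d = (1.960 + 0.842) × √(2/16) = 2.802 × 0.3536 = 0.99 SD

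The exact t-test gives 1.02 SD. The trial is thus sized to detect a difference of about 1 SD.

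**2. Width of the interval for the non-involved hand.** Half-width = t(0.975, df) × √(2/16) × √(1 − ρ²).

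- Unadjusted, df 30: 2.042 × 0.3536 = 0.72 SD
- ρ = 0.5, df 29: 2.045 × 0.3536 × 0.866 = 0.63 SD
- ρ = 0.8, df 29: 2.045 × 0.3536 × 0.600 = 0.43 SD

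**3. Chance of a non-significant result when there is a true deficit.** This is 1 − power from the noncentral t distribution with noncentrality (d / √(1 − ρ²)) × √(16/2).

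| True deficit | Unadjusted | ANCOVA, ρ = 0.5 | ANCOVA, ρ = 0.8 |
|---|---|---|---|
| 0.3 SD | 87% | 84% | 72% |
| 0.5 SD | 72% | 65% | 38% |
| 0.7 SD | 52% | 40% | 11% |
| 1.0 SD | 22% | 12% | under 1% |

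Non-significance is the likelier outcome for deficits below about 0.72 SD unadjusted, 0.62 SD at ρ = 0.5 and 0.43 SD at ρ = 0.8.

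**4. Losses.** The Randomisation section says the list positions of excluded infants are not refilled. With 12 to 14 infants per arm analysed (an assumption), an unadjusted test would miss a 0.5 SD deficit in 78% to 75% of trials.

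**5. What a formal non-inferiority test could do.** Take a one-sided 0.025 test, a true difference of zero and no adjustment. By the normal approximation, power with 16 per arm is Φ(margin/0.3536 − 1.960).

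- Margin 0.5 SD: Φ(−0.55) = 29%
- Margin 0.8 SD: Φ(0.30) = 62%
- Margin 1.0 SD: Φ(0.87) = 81%

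The trial could therefore exclude only a deficit as large as its own planning effect with the usual power.

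**The case against.** The article nowhere says that p>0.05 will count as confirming hypothesis 5. ANCOVA also yields an estimate and an interval, and nothing prevents the investigators from interpreting those. Margins and interval rules are commonly left to a fuller protocol or analysis plan, which is not shown. Hypothesis 5 does not mention harm, and the article answers the restraint concern mainly by design: short daily restraint, free use of both hands at other times, and monitoring of each hand with HAI. The Discussion's remark "If the study hypotheses are confirmed, this project will be of significant value" is a general comment on the project's worth, not a decision rule.

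Most of this stands. A reader might infer that the plan can confirm hypothesis 5 only through a non-significant test. The text does not say so; that rule is an inference from the sole methods stated. A reader might also infer that the trial would most likely declare the hand unharmed whether or not it is. That has no upper bound and goes too far: a 0.7 SD deficit would be missed in 40% of trials at ρ = 0.5, and a 1 SD deficit in 22% or fewer throughout. The absence of a margin is not a fault in itself.

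What remains does not depend on an omitted detail. The article puts a no-difference statement on its list for testing and offers only difference tests and a difference-test sample size. That pairing invites the faulty reading.

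**Conclusion.** The point holds as a matter of wording and interpretation. Following the article, a non-significant comparison could be taken as evidence that the non-involved hand is unaffected, when the interval would still include deficits of moderate size. A true 0.5 SD deficit would go undetected in about 72% of trials unadjusted, 65% at ρ = 0.5 and 38% at ρ = 0.8. Deficits of about 1 SD would usually be found.

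These figures rest on SD units, assumed correlations and full follow-up of 16 per arm. The primary efficacy comparison, the randomisation and the data collection are unaffected, so this should be corrected before analysis but does not threaten the trial.

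**What to change.** Reword hypothesis 5 as an estimation question: how far does development of the non-involved hand differ between the groups? Report the between-group difference in non-involved-hand HAI change with its 95% confidence interval from the planned ANCOVA. State that p>0.05 will not be read as showing no difference or no harm, that the conclusion rests on the size of deficit the interval excludes, and that an inconclusive result is allowed.

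A non-inferiority margin is optional. It is worth adding only if it can be justified before unblinding, which is difficult because the article describes HAI as still under development and gives no SD or important difference for it. At 16 per arm, a margin well below 1 SD would often end inconclusively.

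The change needs no extra infants, visits or data. Its cost is that hypothesis 5 may have to be reported as inconclusive.
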